## Abstract

**Background:**

World-wide healthcare systems are faced with an epidemic of type 2 diabetes. In the United Kingdom, clinical care is primarily provided by general practitioners (GPs) rather than hospital specialists. Intermediate care clinics for diabetes (ICCD) potentially provide a model for supporting GPs in their care of people with poorly controlled type 2 diabetes and in their management of cardiovascular risk factors. This study aims to (1) compare patients with type 2 diabetes registered with practices that have access to an ICCD service with those that have access only to usual hospital care; (2) assess the cost-effectiveness of the intervention; and (3) explore the views and experiences of patients, health professionals and other stakeholders.

**Methods/Design:**

This two-arm cluster randomized controlled trial (with integral economic evaluation and qualitative study) is set in general practices in three UK Primary Care Trusts. Practices are randomized to one of two groups with patients referred to either an ICCD (intervention) or to hospital care (control).

**Intervention group:** GP practices in the intervention arm have the opportunity to refer patients to an ICCD - a multidisciplinary team led by a specialist nurse and a diabetologist. Patients are reviewed and managed in the ICCD for a short period with a goal of improving diabetes and cardiovascular risk factor control and are then referred back to practice.

or

**Control group:** Standard GP care, with referral to secondary care as required, but no access to ICCD.

Participants are adults aged 18 years or older who have type 2 diabetes that is difficult for their GPs to control. The primary outcome is the proportion of participants reaching three risk factor targets: HbA_1c_ (≤7.0%); blood pressure (<140/80); and cholesterol (<4 mmol/l), at the end of the 18-month intervention period. The main secondary outcomes are the proportion of participants reaching individual risk factor targets and the overall 10-year risks for coronary heart disease(CHD) and stroke assessed by the United Kingdom Prospective Diabetes Study (UKPDS) risk engine. Other secondary outcomes include body mass index and waist circumference, use of medication, reported smoking, emotional adjustment, patient satisfaction and views on continuity, costs and health related quality of life. We aimed to randomize 50 practices and recruit 2,555 patients.

**Discussion:**

Forty-nine practices have been randomized, 1,997 patients have been recruited to the trial, and 20 patients have been recruited to the qualitative study. Results will be available late 2012.

**Trial registration:**

[ClinicalTrials.gov: Identifier NCT00945204]

## Background

Configuring services so that all people with type 2 diabetes mellitus (T2DM) can benefit from good quality, target-driven and patient-focused care is a major challenge to healthcare systems such as the UK National Health Service (NHS), especially given the increased and increasing prevalence. In recent years there has been a shift in place of care from hospital to general practice [1]. Although the new contract for general practices set targets for the control of diabetes, concerns were voiced about whether primary care could continue to cope without additional support [2]. Currently, about 70 to 80% of people in the United Kingdom (UK) with T2DM are managed entirely in primary care. There is long-standing and continued evidence of deficiencies in provision of care and significant variations between general practices [3,4]. More recently, differences in quality of care and outcomes have been reported depending on the model of care adopted or staff levels of experience [5,6]. Practices in areas of high deprivation and mix of ethnicity are less likely to achieve adequate levels of control [7-9].

There is evidence from randomized controlled trials that intensive management of T2DM can reduce complications such as retinopathy, nephropathy and neuropathy, as well as reducing the risk of cardiovascular disease [10]. Benefits are seen from improved glycemic control, lower blood pressure and better management of lipids [11-13]. Patients with improved glycemic control also consistently report better functional status and wellbeing [14-16].

It is less clear how benefits seen in individual explanatory trials might be realized in a new integrated service model. A Cochrane review found evidence that structured recall, patient education, and support from specialist nurses can lead to better outcomes [17], and a trial in Danish general practice found that intensive patient-focused management led to significant risk reduction [18]. Economic modeling also suggests that intensive control of risk factors is likely to be cost-effective in the UK [19]. Although the evidence indicates that access to multidisciplinary, community-based services can support general practices in achieving good clinical control of their diabetic patients, and possibly improve patient outcomes, it is unclear what the optimum combination or model might be for service provision.

One method suggested is introduction of intermediate care clinics for diabetes (ICCD). The intermediate care model aims to deliver high-quality care nearer to the patient through multidisciplinary, locality-based teams, with the added opportunity for developing professional expertise in the community and hopefully reducing care costs. A common approach is for medical care to be provided by general practitioners (GPs) with a special interest (GPwSI) in diabetes [20] working with community-based specialist teams. ICCDs began to be introduced in the UK in 2004. A descriptive evaluation found that intermediate care clinics were popular with patients and practitioners and appeared to reduce outpatient attendances by 25% [21]. However, inherent in the ICCD model is a trade-off between the higher levels of technical expertise available in the clinic versus a reduction in the continuity of care as previously provided solely by the GP practice. Continuity of care has been shown to be related to glycemic control [22]. The costs of the two models will also differ, and the cost-effectiveness of ICCD introduction remains unclear.

To date, there have been a number of other ICCD services established in the UK, although the staffing and organization of these varies and none has been introduced under trial conditions with an integral economic evaluation. One service, set up in Cardiff, Wales, has reported some consideration of costs and benefits, although no data on the impact of this ICCD model on costs and patient outcomes are available [23]. Other initiatives include Somerset Community Health [24]; an ICCD service established in Southampton [25]; and an ICCD team set up in Lambeth, London [26]. The latter has reported that the service is marginally cost saving [27]. No other evaluations have been published.

The present study protocol describes a cluster randomized controlled trial of an ICCD intervention set up in three Primary Care Trusts (PCTs) to improve outcomes for primary care patients with T2DM. In accordance with the Medical Research Council’s framework for development and evaluation of complex interventions the trial intervention built on published and ongoing formative research [28,29].

Practices recruited to the study are randomized to either usual care or intervention arm, with the latter having access to the new ICCD clinics. In participating practices, patients with T2DM are invited to take part in the trial. Recruited patients in both arms are given a baseline assessment by a study nurse. This includes measurement of HbA_1c_, body mass index (BMI), waist circumference, blood pressure, urine and lipids. Participating patients are asked to attend a follow-up assessment 18 months after their baseline assessments, when the same measurements are repeated. Questionnaires about quality of life, satisfaction with current services, continuity of care and health service use and personal costs are completed at baseline and follow-up. An integral economic evaluation measures costs in both groups, with a comparative assessment of marginal costs and outcomes. To deal with possible selection bias, risk factor control of all patients with T2DM in intervention and control practices will be compared using anonymised GP data. Additionally, a qualitative study is exploring the views of patients, health professionals and other stakeholders using semi-structured interviews.

The overall aim is to conduct a randomized controlled trial to evaluate the effectiveness and cost-effectiveness of community-based intermediate care clinics in the management of T2DM. Specific objectives are to:

1. Compare the following in patients with T2DM registered with practices that have access to ICCD with those that have access only to usual care:

·control of cardiovascular risk factors including glycemic, blood pressure and lipid control, and cardiovascular risk assessed by UKPDS risk engine;

·quality of life;

·satisfaction with services and continuity of care;

·referral patterns and non attendance rates;

·annual cost per patient with diabetes.

2. Estimate the difference in the cost of the resources used by patients in each arm of the trial, and the cost-effectiveness of the ICCD intervention.

3. Explore the views and experiences of patients, health professionals and other stakeholders.

## Methods/Design

### Study design

This pragmatic trial is a two-arm parallel group cluster randomized controlled trial, with randomization at the GP practice level. Practices recruited to the study are randomized to the intervention or control arm. Practices in the intervention arm have access to ICCD. Those randomized to usual care are issued with local guidelines and continue to manage their patients, including hospital referrals, in the usual way. All patients with T2DM in participating practices are eligible for inclusion in the study; up to 100 patients per practice will be recruited. Patients consenting to take part are asked to attend a baseline assessment and then a follow-up assessment at the end of the 18-month intervention period. The trial will assess differences in the percentage of patients achieving adequate control of HbA_1c_, cholesterol and blood pressure (combined) among patients who have access to ICCD in comparison with patients receiving standard care. The study is also designed to examine the effect of access to an ICCD on process measures such as contacts with hospital services and general practice. Additionally, semi-structured interviews are being undertaken in the intervention arm to explore the views and experiences of patients, health professionals and other stakeholders. The study design is shown in Figure 1.

**Figure 1 F1:**
[figure not shown]
Study design and flow chart.

The study protocol was approved by Trent Multi-centre Research Ethics Committee (REC Ref 06/MRE04/41), with amendment to sample size accepted in August 2006.

### Sample size

We initially planned to recruit a total of 5,000 patients from 51 practices (25 in one trial arm, and 26 in the other), with approximately 100 patients being recruited from each practice. Due to losses during follow-up, we expected the final number of patients in each practice to be 72, or approximately 3,700 patients in total.

Estimates for the percentage of patients achieving control in the usual care group are taken from a UK survey [4]. We used HbA_1c_ for our primary sample size calculation as this is the outcome variable for which there is the most robust information on intra-class correlation (ICC). To detect a difference of percentage well-controlled (HbA_1c_ <7.5%) from 50% in the control group to 60% in the intervention group (α = 0.05, Power = 0.8not allowing for clustering, requires a sample size of 408 subjects in each arm. Using an Intra-class correlation (ICC) of 0.047, and with 72 patients in each cluster, the necessary sample size in each arm is 1770, representing a total of 3,540 patients for both arms. This number is also adequate to detect a 10% difference in cholesterol control (from 60% to 70%) and blood pressure control (from 60% to 70%). Estimates of ICC for blood pressure and cholesterol are taken from the UK Asian Diabetes Study (UKADS), a study of care provision for people of South Asian ethnicity with diabetes [30]. Assuming the ICC for our combined primary outcome (adequate control of HbA1C, blood pressure and cholesterol) is 0.05 and achievement is at 20% in the control arm and 30% in the intervention arm, we would need a total of 2,848 patients.

During the recruitment phase, it became clear that we would fall short of the intended 5,000 patients, and of the expected 72 patients per practice. A revised sample size estimate of 40 patients in each practice after follow up (approximately 2,000 patients in total) was proposed and accepted by the ethics panel. Using the same ICC values as previously, and considering the primary outcome, the necessary sample size in each arm is 1,022, for a total of 2,044 (note that this is the necessary sample size for patients retained at follow-up; the sample size for initial recruitment must therefore be larger, or according to our estimates, at least 2,555). This value is approximately sufficient to give power of 80% to detect a 10% difference for both the combined primary outcome and control of blood pressure. We can restore the power to that of the original protocol, before the changes to sample size were made, by considering the detection of a 12% difference for these measures. For control of HbA_1c_ and cholesterol the power is slightly less than 80%.

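### The revised 1,022 per arm (2,044 in total) does not follow from the primary-outcome inputs it is attributed to; those give 924 per arm (1,848), so the figure is about 11% too high for that outcome

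*Protocol article*

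**What the plan says.** All of this is in the Sample size section of the protocol article.

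- **Original calculation, HbA1c.** For 50% v 60% controlled, the section states "α = 0.05, Power = 0.8not allowing for clustering, requires a sample size of 408 subjects in each arm". With an ICC of 0.047 and 72 patients per practice this becomes 1,770 per arm, 3,540 in total.
- **Original calculation, primary outcome.** The rates are given as "achievement is at 20% in the control arm and 30% in the intervention arm". The composite is assigned an assumed ICC of 0.05, and the total comes out at 2,848.
- **Revision.** The number retained per practice falls to 40. The ICCs are said to be unchanged and the calculation is said to be for the primary outcome: "the necessary sample size in each arm is 1,022, for a total of 2,044". At least 2,555 must then be recruited, and the abstract repeats 2,555 as the aim.
- **Power claims.** The revised number is called "approximately sufficient to give power of 80% to detect a 10% difference for both the combined primary outcome and control of blood pressure". The section adds that the power of the original protocol can be recovered "by considering the detection of a 12% difference for these measures".

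**The concern.** Only the cluster size is said to have changed, from 72 to 40. The revised number should therefore be the original one with a smaller design effect, and it is not. A reader cannot reproduce the central sample-size figure from the inputs given for it.

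The figure matters because 2,555 is derived from it, and the 1,997 patients actually recruited will be judged against 2,555. The published shortfall is 2,555 − 1,997 = 558. On the primary-outcome inputs it is 2,310 − 1,997 = 313. Someone interpreting a null result would think the trial further below its own requirement than its assumptions imply.

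**Working it through.** **Inputs (Sample size section).** α = 0.05, taken as two-sided because that reproduces 408; power 0.80; primary outcome 20% v 30%, ICC 0.05; HbA1c 50% v 60%, ICC 0.047; blood pressure control 60% v 70%, ICC not given; cluster size m = 72 originally, 40 in the revision.

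**Formulas.** With d the difference and p̄ the mean of the two proportions:

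- n = [1.96·√(2p̄(1−p̄)) + 0.8416·√(p1(1−p1)+p2(1−p2))]² / d²
- continuity-corrected n = (n/4)·[1+√(1+4/(n·d))]²
- design effect DE = 1+(m−1)·ICC

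**Step 1: reproduce the original figures.**

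- HbA1c: corrected n = 407.1, rounded up to 408 (stated 408).
- HbA1c clustered: 408 × (1+71×0.047) = 408 × 4.337 = 1,769.5, so 1,770 (stated 1,770).
- Primary outcome: corrected n = 312.8, so 313; 313 × (1+71×0.05) = 313 × 4.55 = 1,424 per arm, 2,848 in total (stated 2,848).

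**Step 2: same method, m = 40.** 313 × (1+39×0.05) = 313 × 2.95 = 923.35, so 924 per arm and 1,848 in total. (Rounding to the nearest whole number gives 923 and 1,846, which changes nothing.) The stated 1,022 exceeds 924 by 98/924 = 10.6%.

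**Step 3: can another convention reach 1,022?** For 20% v 30%:

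| Variant | Per arm |
|---|---|
| No continuity correction | 294 × 2.95 = 868 |
| ICC 0.047 | 313 × 2.833 = 887 |
| m = 41 | 313 × 3.00 = 939 |
| Rounded up to whole practices of 40 | 960 |
| 90% power | 412 × 2.95 = 1,216 |

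None does. With n = 313, reaching 1,022 needs an ICC of (1,022/313 − 1)/39 = 0.058, or a cluster size of 1 + (1,022/313 − 1)/0.05 = 46.3.

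**Step 4: recruitment.** 2,044/2,555 = 0.80, so a 20% loss is implied. At that loss, 1,848/0.80 = 2,310.

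**Step 5: primary-outcome power.** Power = Φ{[d − 1/nₑ − 1.96·√(2p̄(1−p̄)/nₑ)] / √[(p1(1−p1)+p2(1−p2))/nₑ]}, where nₑ is the number per arm divided by DE. The uncorrected version omits 1/nₑ.

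| Design | nₑ per arm | Difference | Power, corrected (uncorrected) |
|---|---|---|---|
| 2,044, m = 40 | 346.4 | 10 points | 84.1% (86.1%) |
| 2,044, m = 40 | 346.4 | 12 points | 94.2% (95.1%) |
| 2,848, m = 72 | 313.0 | 10 points | 80.0% (82.5%) |
| 3,540, m = 72 | 389.0 | 10 points | 88.2% (89.8%) |
| 3,700, m = 72 | 406.6 | 10 points | 89.6% (91.0%) |

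**Step 6: a possible origin.** For blood pressure control, 60% v 70% gives a corrected n of 376. An assumed ICC of 0.044 gives 376 × (1+39×0.044) = 376 × 2.716 = 1,021.2, so 1,022.

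**The case against.** The strongest reply is that the number is sound and only its label is wrong. The section makes the same figure serve blood pressure control as well, and Step 6 shows that an ICC of 0.044 would produce exactly 1,022. The surrounding text fits. At that ICC, blood pressure would have needed about 1,551 per arm at m = 72, inside the 1,770 called adequate. HbA1c power at 1,022 per arm is 75–77%, which agrees with the remark that it falls slightly below 80%. Simply substituting 924 would cut blood pressure power to about 76% (at that assumed ICC) and HbA1c power to about 70%, and so contradict the neighbouring sentences.

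This stands as a warning about the remedy. It does not rescue the sentence, which attributes the figure to the primary outcome. The ICC of 0.044 appears nowhere in the article, so this origin remains an inference.

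Three stronger readings may tempt a reader, and the article does not support them:

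- **That the 12-point sentence is false.** Power at 12 points (94–95%) is at least the original power whichever original is meant: 80%, 88–90% or 90–91%. With about 2,000 retained, 11 points gives 89.4% against 89.6% for the 3,700 plan (both corrected), so 12 is the first whole point to reach it. The sentence is imprecise: it does not say which original power it means, and a larger target difference does not restore power for the 10-point difference that the primary outcome section still sets as the aim.
- **That 2,044 was the figure put to the ethics committee.** The section says the panel accepted 40 per practice after follow-up, about 2,000 in total.
- **That the 80% power statement is untrue.** It claims approximate sufficiency for 80%, and 84% is sufficient. It understates the primary-outcome power without contradicting it.

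**Conclusion.** The point holds for the number and its attribution. On the stated inputs the primary outcome needs 924 per arm (1,848 retained), against a published 1,022 (2,044). The excess is about 11%, and it passes into the 2,555 in the Sample size section and the abstract. The error is conservative, since it asks for more patients than the primary outcome needs and leaves that outcome with 84–86% power at 2,044. Trial conduct, the analysis and the type I error are unaffected.

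This rests on a two-sided 5% test, equal arms, equal cluster sizes and the continuity-corrected formula. That method is well supported because it returns all three original figures. Dropping the correction lowers the requirement to 868 and widens the gap. The blood pressure part of the power and 12-point statements cannot be checked, because its ICC is not given.

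**What to change.** In the Sample size section, do one of two things:

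1. State that the primary outcome needs 924 per arm, 1,848 retained and 2,310 recruited at 20% loss (80% power, 20% v 30%, ICC 0.05, 40 per practice), and revise the neighbouring statements on blood pressure, HbA1c and cholesterol power to match.
2. If 1,022, 2,044 and 2,555 are kept because another endpoint drives them, name that endpoint and its ICC, remove the attribution to the primary outcome, and give the primary-outcome power at 2,044 as about 84%.

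In either case:

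- Make the abstract agree.
- Replace the 12-point sentence with the primary-outcome power at 2,044 for 10 points (84–86%) and 12 points (94–95%). Name the original power used for comparison: 80% at 2,848, 88–90% at 3,540 or 90–91% at 3,700.

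The cost is a text correction. The second option also requires the sponsor to retrieve the ICC that was used.

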### Setting/ participants

The study is taking place in general practices in three PCTs in a geographically and socially diverse sub-region of England. Providing good quality care for people with diabetes is a particular challenge for the health services in these areas given the prevalence of the condition, particularly in minority ethnic groups.

#### Practices

All GP practices in the three participating PCTs were first invited to express an interest in participating in the trial. Experience from a similar trial of community cardiology clinics in Leicester suggested that over 80% of practices would agree, as it gives them an even chance of accessing an additional service for their patients [31]. The aim was to recruit 51 practices in total (52% of all eligible practices).

#### Patients

To be eligible for inclusion in the trial, potential participants must be patients in a participating practice, as well as:

a) be adults aged 18 years or older;

b) have T2DM;

c) not have severe cognitive impairment which would preclude active engagement in the trial;

d) not be pregnant at recruitment

e) not have a severe mental illness (for example, anxiety or depression, which would preclude active engagement in the trial);

f) not be receiving terminal care;

g) receive a letter of invitation to the study from their practice;

h) express a wish to participate and provide written consent.

### Study intervention

Following development work, community-based ICCDs were established in the participating PCTs. These are designed to work closely with hospital-based specialist teams and community services, including podiatry and dietetics, in order to support primary care, particularly smaller practices that have the most difficulty achieving good control for their patients. Each ICCD consists of a multidisciplinary team, led by a specialist nurse, with emphasis placed on education and self-management. Medical care is provided by a diabetes specialist or a GP with a special interest (GPwSI) in diabetes and, in practices with access to the service, patients with T2DM are no longer referred to hospital directly. Guidelines for referral to the ICCDs are common across all sites, and include people with poorly controlled T2DM and those with poorly controlled cardiovascular risk factors. Patients are managed by the ICCD team until control of risk factors is achieved and then participants are referred back to primary care. The team members work to local guidelines, adapted from national evidence-based guidelines [32].

At both sites the planned capacity is for 20% of patients with T2DM to attend the ICCD per annum, assuming that on average patients will be seen four times in the ICCD before returning to primary care.

